### Setting

The KwaZulu-Natal (KZN) province has an HIV prevalence of 15.8% for all people over 2 years of age, the highest prevalence of HIV in the country [3]. Clinics in the *Masihambisane *project are spread over three districts in KZN (see Figure 1). Antenatal clinic data from these districts indicates that in 2007, prevalence was 40.8%, 34.1% and 41.6% [37]. Nineteen clinics that did not have on-going interventions were considered for the study sample based on proximity to main research site, type of clinic (either a community health clinic or primary health care clinic), availability of antenatal and postnatal services at the clinic, and uptake of antenatal and postnatal services (with a minimum of 300 women per annum). Table 1 lists the characteristics examined to establish the eight clinics most suitable for inclusion.

**Figure 1 F1:**
[figure not shown]
**Geographic location of Mashihambisane clinics**.

**Table 1 T1:** Characteristics evaluated prior to clinic selection.

Characteristic	Description
**Type of Clinic**	Community Health Centre offers wide array of services 24 hours per day; Primary Health Care Clinic offers delivery of primary health care 8 am-5 pm daily; Mobile Primary Health Care Clinic offers delivery of primary health care through mobile unit 8 am-5 pm daily.

**Size of Clinic**	Determined by the type and scope of maternal and child services, including antenatal, post natal, PMTCT, and the number of first and repeat clinic attendees each month.

**Geographic Location**	Determined by logistical feasibility, availability for telecommunication network communication signal & space available for research activities.

**Risk of Contamination**	Control group is determined to be at no- or low-risk for contamination of intervention activities.

### Research Ethics and Approval

The Institutional Review Board of the University of California, Los Angeles (UCLA, G06-05-062) and the Research Ethics Committee of the Human Sciences Research Council in South Africa (HSRC, REC 4/07/03/07) have approved the study and oversee adherence to the study protocol over time. A six-member Data Safety and Monitoring Board (DSMB), consisting of local and international experts, monitors the implementation of the trial. National, provincial, district, and municipal health authorities approved the study and its protocol, and set the conditions of the standard care practice. Quarterly meetings are held with a Community Advisory Board (CAB) consisting of 25 local stakeholders who serve as liaison between research staff and the community, advising on study policies and keeping the community informed of progress. Regular feedback meetings are held with health authorities.

### Research activities and procedures

#### Pilot activities

*1. Clinic selection and matching criteria*. Geographic maps, administrative data from the health district, and a month-long observational period in each clinic provided information necessary for selection of clinics for study inclusion. Clinics were identified on the following criteria: a) location - rural (n = 4) or urban (n = 4); b) clinic type - community (n = 2) or primary health care centre (n = 6); c) size of catchment area; d) monthly census of pregnant women; and e) resources such as space, staffing, and transport.

*2. Piloting of the assessment and the intervention*. All instruments and intervention sessions were piloted through focus groups and key informant interviews. These pilot activities involved officials from the KZN Department of Health, including Cluster Heads, District Managers, Medical Managers and Programme or Clinic Managers, Department of Health Clinic Service Providers, and clinic staff members. WLH also participated in pilot sessions of the planned intervention.

*3. Programming and bench testing of mobile phones for collection of assessment interviews*. Data is collected on mobile phones running a survey software package (Mobile Researcher; http://www.populi.net/mobileresearcher/). This platform allows the phone to be used to collect and upload numeric, voice and text data. Two models of phones were used in the pilot - the Nokia E61i (a business phone similar to a PDA) and the Nokia 2630 (an inexpensive candybar phone). Initial training covered practical aspects of phone navigation, checking for software updates, use of the software, and uploading data to the central server. Staff spent two weeks familiarising themselves with the baseline survey on the phone. During this time multiple tests were run to ensure that all data entered on the phone was correctly uploaded and that the response entered on the mobile corresponded to the value stored in the database.

*4. Standardization of clinic procedures and training updates consistent with national guidelines*. During clinic observations, processes for antenatal registration, routine HIV testing, post-test counselling, and antenatal care were identified. The team, health administrators, and clinic staff spent two months collaboratively standardizing and training clinic staff in these procedures. The re-training focused on ensuring that all personnel were equipped to deliver standardised and routine PMTCT antenatal and postnatal health care, as prescribed by current departmental policies and guidelines. Strategies to increase HIV Voluntary Counselling and Testing (VCT) service delivery and uptake were also implemented in all clinics.

### Study Procedures

#### Recruitment

A protocol was written for each clinic to ensure that recruitment was standardized across clinics despite differences in procedures. The intake nurse in the antenatal clinic services introduces the *Masihambisane *research assistant to pregnant women in the waiting room, and the women are provided with a brief overview of the study and key PMTCT messages.

HIV VCT is conducted during the first antenatal visit using an opt-out procedure. During counselling by a clinic nurse, all women, regardless of HIV status, are offered the opportunity to speak to *Masihambisane *staff. *Masihambisane *is branded as a program to support pregnant women, not specifically WLH. The *Masihambisane *staff member reinforces key PMTCT messages tailored to each woman's HIV status. In intervention clinics, the staff member also offers all women, HIV-positive and HIV-negative, a referral to speak with a Peer Mentor for additional support regarding their pregnancy, health or HIV status.

In the case of WLH, the Peer Mentor discloses her own serostatus, empathizes with the WLH and offers follow-up for enrollment into the research study. The WLH is given material about the study and the consent form to read carefully at home. At a second enrollment meeting, the research assistant reads aloud a script that describes the research study, probing for the WLH's understanding of key concepts. Women are reassured that her decision to enroll will not affect services received at the clinic. With voluntary informed consent, a baseline interview is conducted using the mobile phone to collect and record data. In the intervention clinics, the WLH is then referred to the Peer Mentor for enrollment into the small group support programme.

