## Methods/Design

### Objectives

*Masihambisane *is a cluster RCT to test the effectiveness of Peer Mentor support in addressing health, mental health, and stigma challenges faced by WLH. The challenges of chronic illnesses, mental health symptoms, infant feeding and treatment are confronted by WLH on a consistent, daily basis, therefore no single outcome can definitively validate the effectiveness of this Peer Mentor program. We focus on cumulative change across 15 indicators of maternal and infant health. The health-protective behaviors of WLH are documented over time and compared to the baseline rates. These indicators range in their uptake, for example, 92% of babies receive their vaccinations on time, however, infant HIV testing and receipt of results occurs less frequently.

We hypothesize that WLH and their infants in the intervention clinics, compared to WLH who receive standard PMTCT care, will have:

- higher maternal knowledge about HIV self-management;

- better maternal ARV adherence antenatally and at the time of birth;

- increased HIV testing of their baby at six weeks and receipt of test results;

- adherence to regular health visits and TB testing;

- infant weight of more than 2500 grams at birth with normal growth and development for 12 months;

- greater mental health, social support, and ability to cope with HIV stigma;

- higher rates of HIV testing among sexual partners; and

- higher rates of condom use with partners of serodiscordant HIV status.

In order to achieve statistical significance in the analyses, we need to recruit 1200 pregnant WLH (150 per clinic at 8 clinics) with 600 in the intervention and 600 in the standard-of-care control clinics. Enrollment criteria are: 18 years or older at the time of first assessment, less than 34 weeks pregnant at intake, HIV seropositive, and enrolled in the PMTCT programme at one of the eight study clinics. In addition, prospective participants are asked to indicate their intention to reside in the area for the duration of the study, and they must be able to give informed consent, as judged by the interviewer.

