### Design

Eight rural clinics in Kwa-Zulu-Natal were matched on information collected from clinic surveys and observations regarding client load, patient characteristics, range of services offered, and rural-urban setting. The UCLA team, without first-hand experience of the clinics, then randomized clinics to the intervention or the standard care condition.

Standard care includes: dual therapy for PMTCT, referral to Highly Active Anti-Retroviral Therapy (HAART) for women with CD4 counts below 200 or WHO Stage 4 illness, infant PCR test results by six weeks of age, and co-trimoxazole for exposed infants starting at six weeks of age [36]. The intervention clinics will receive the standard care in addition to Peer Mentor support sessions. Peer Mentors were selected from the local communities, based on their HIV seropositive status and role as positive peer deviants. Peer Mentors were trained to deliver four antenatal and four postnatal small group sessions in the clinics to supplement the PMTCT program. An independent assessment team conducted in-person interviews with WLH during pregnancy, and within six weeks, six months and twelve months post-birth, evaluating each WLH and her baby's health and well-being.

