#### *Masihambisane *Intervention

The Peer Mentors work full-time in the intervention clinics and are integrated into the Department of Health PMTCT programme at each site. WLH are invited to attend a series of four antenatal and four postnatal sessions, scheduled to coincide with their routine antenatal and well-baby clinic visits. Sessions last 60 to 90 minutes, and are attended by four to ten WLH who meet to discuss, roleplay, share, and practice strategies to address issues critical to effective PMTCT. Each session proceeds in a similar sequence: WLH arrive, sing and pray together, and share successes and joys from their week. The Peer Mentor shares her triumphs and challenges as a WLH and acknowledges the importance of the support group for her. A topic is introduced for the day's meeting and a brief demonstration of the content message is presented, then the group brainstorms the types of challenges the WLH will encounter if she tries to implement this knowledge in her life. Finally, goals are set for the upcoming week and a song and a prayer end the meeting.

Each of the following issues is covered by the intervention:

1) *Living Positively*. Using a jar with different coloured jelly beans, the Peer Mentor shows that all families in KwaZulu-Natal are affected by HIV and the WLH is not alone, in particular she has support in the group leader and group members. WLH are encouraged to attend all clinic appointments. Women are provided with referral letters to the couple to encourage them to get tested together for STIs. Women discuss to whom they want to disclose their serostatus and roleplay the process of disclosure and asking for emotional support.

2) *Keeping Myself and My Baby Healthy*. The Peer Mentor helps WLH understand why they must avoid smoking and drinking, eat healthily, take vitamins and medicine as prescribed in antenatal care, get regular exercise, seek and maintain social support, and do things they enjoy. A realistic black baby with Fetal Alcohol Syndrome is presented and the characteristics and life-long consequences of alcohol on babies are discussed. A raw egg is broken in a cup of alcohol and women watch as the egg poaches at room temperature to illustrate adverse effects of alcohol on brain development *in utero*.

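### In intervention clinics only, women may meet a Peer Mentor who opens the way to enrolment before consent and baseline, so who enrols and the psychosocial baseline can differ by arm

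*Protocol article*

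**What the plan says.** Under Design, allocation is by clinic and precedes recruitment: "The UCLA team, without first-hand experience of the clinics, then randomized clinics to the intervention or the standard care condition". Under Masihambisane Intervention, "The Peer Mentors work full-time in the intervention clinics".

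Recruitment then gives this order:

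1. In all clinics, a research assistant gives waiting-room information about the study, and women may talk to project staff.
2. One step is confined to one arm: "In intervention clinics, the staff member also offers all women, HIV-positive and HIV-negative, a referral to speak with a Peer Mentor for additional support".
3. For a woman with HIV, "the Peer Mentor discloses her own serostatus, empathizes with the WLH and offers follow-up for enrollment into the research study". She takes the study material and consent form home.
4. At a second meeting the research assistant reads a script and checks understanding. "With voluntary informed consent, a baseline interview is conducted using the mobile phone to collect and record data".
5. In intervention clinics she is then referred to the Peer Mentor for the group programme.

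The same section says that a recruitment protocol was written for each clinic to standardise the process.

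On the use of baseline, Objectives says: "The health-protective behaviors of WLH are documented over time and compared to the baseline rates". Data Analysis compares the composite score over 12 months between conditions in multilevel models. It mentions neither a comparison of enrolment by arm nor adjustment for enrolment differences.

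**The concern.** Randomising clinics balances clinics, in expectation. It does not balance which women within them agree to take part, because consent is sought after the arm is known on site. The enrolment route here has an extra step in one arm, delivered by the person whose support is being tested. That can act in two ways.

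- **Selection.** An empathic invitation from an HIV-positive peer may bring in different women from those who enrol without it. Any resulting difference in prognosis is read as an intervention effect, or hides one.
- **Baseline.** Background argues that peer support around the time of diagnosis is itself powerful. If so, a first dose of the tested ingredient may precede the intervention-arm baseline. The measures most open to this are mental health, social support and coping with stigma, which are among the trial's hypotheses. A contrast built on change from that baseline, or adjusted for it, would give away part of the effect.

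**Working it through.** **The plan's own figure.** 8 clinics × 150 = 1200 and 4 × 150 = 600 per arm; both agree with Objectives. No alpha, power, effect size, SD or ICC is given, so there is no power calculation to reproduce. The point rests on the order of procedures. The arithmetic only shows what size of error could follow.

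**Order of procedures.** The sentence about the Peer Mentor's disclosure does not itself name an arm. The sentence before it limits the referral to intervention clinics, and that is where Peer Mentors are said to work. No counterpart to this step is described for control clinics. The general statement about standardised recruitment stands beside the arm-specific step and does not remove it.

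**Illustration 1: selection, true effect zero.** From the document: 600 per arm, 150 per clinic, 8 clinics. Assumed: 50% of eligible women enrol in one arm and 70% in the other; correlation r between willingness to enrol and outcome of 0.2 to 0.4; ICC 0.01, 0.02 or 0.05.

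If the most willing fraction p enrols, mean willingness among enrolees is φ(z_p)/p, where z_p cuts off the upper fraction p of a standard normal.

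- p = 0.50 gives 0.798; p = 0.70 gives 0.497; difference 0.301.
- Shift between arms = r × 0.301 = 0.06, 0.09, 0.12 SD for r = 0.2, 0.3, 0.4.

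Standard error of the arm difference in SD units = √(2 × [1 + 149 × ICC] / 600). Two-sided rejection comes from the noncentral t on 8 − 2 = 6 df with noncentrality shift/SE:

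| ICC | Design effect | SE | r = 0.2 | r = 0.3 | r = 0.4 |
|---|---|---|---|---|---|
| 0.01 | 2.49 | 0.091 | 8.7% | 13.4% | 20.1% |
| 0.02 | 3.98 | 0.115 | 7.3% | 10.2% | 14.4% |
| 0.05 | 8.45 | 0.168 | 6.1% | 7.4% | 9.4% |

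**Direction.** In this model the arm that enrols more takes in more of the less willing women, so its mean is lower. If that is the intervention arm, nearly all the excess rejections suggest harm. False claims of benefit fall from 2.5% to 0.1-0.6% at ICC 0.01 and to 0.2-0.8% at ICC 0.02. If the contact instead attracts more motivated women, the sign reverses.

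**Illustration 2: exposed baseline.** Assume that the contact shifts the baseline score by d = 0.1 to 0.2 SD and that baseline and outcome correlate 0.3 to 0.7. A change-from-baseline contrast loses d, that is 0.1 to 0.2 SD. A baseline-adjusted contrast loses correlation × d, from 0.3 × 0.1 = 0.03 to 0.7 × 0.2 = 0.14 SD.

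**The case against.** Much of the other side's case is sound.

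- **The contact is optional.** Staff offer a referral. The article does not say that every woman accepts, or that contact is a condition of enrolment. A reader might infer that all intervention women are exposed before baseline; the text supports only that some may be. This stands.
- **Much of the route is common.** The waiting-room overview, the talk with project staff, and the scripted consent meeting are not limited to one arm, and the clinic-level recruitment protocols are not shown. The capacity check, "they must be able to give informed consent, as judged by the interviewer", is an eligibility criterion for both arms and is no evidence of a difference. This narrows the point but leaves the extra step before consent.
- **No analysis of change is specified.** Data Analysis lists post-birth assessments and compares conditions over 12 months. The remark in Objectives about baseline rates is descriptive. Many composite items, such as birth weight, infant prophylaxis and the six-week infant test, have no antenatal baseline and cannot be diluted. This stands and confines the baseline concern to the psychosocial measures.
- **The numbers are assumed.** A reader might take the raised rejection rates to mean a trial biased towards finding benefit. The documents support no direction, and in the illustration higher intervention enrolment works against the intervention. This stands.
- **Enrolment is monitored.** Under Data Collection, clinic counts include HIV tests, results received and participants enrolled. These can reveal unequal uptake but do not prevent or correct it.

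**Conclusion.** The point holds as a design weakness that allows bias, not as a demonstrated bias. Recruitment sets out a sequence that differs by arm before consent and baseline, and nothing in Data Analysis answers it. Enrolment, and the mental health, support and stigma baselines, can differ by arm as a result.

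It would go too far to say that they do differ, or that the trial's result is biased in a known direction. The article gives no enrolment fractions, no acceptance rate for the referral and no effect of the contact.

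On the assumed inputs, the spurious difference is 0.06 to 0.12 SD, with two-sided rejection of about 9-20%, 7-14% and 6-9% at ICC 0.01, 0.02 and 0.05. The sign depends on which women the contact brings in. This should be fixed. The sequence is clear from the text; confidence that it produces material bias is medium.

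**What to change.** **For remaining enrolment.** Use the same research-assistant invitation and script in all eight clinics. Complete consent and the baseline interview before a prospective participant's Peer Mentor contact. The existing post-baseline referral already provides the place for that contact.

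**For all participants.**

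- Adjust the primary comparison for characteristics that the contact cannot alter: age, gestation at first visit and first CD4 count. Age and gestation are needed for eligibility, and CD4 is taken from the records.
- Do not use change from the possibly exposed psychosocial baseline, or adjustment for it, as the main contrast.
- Compare the enrolled fraction of HIV-positive women by arm from the clinic counts under Data Collection. The listed counts do not name HIV-positive women separately, but they are said to allow monitoring of those receiving PMTCT, which can serve as the denominator.

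**Cost.** The work is a script amendment and some model wording, but it has real drawbacks. Contact near diagnosis, which is part of the rationale in Background, is delayed for prospective participants. Discussion refers to the trial's first year, so a change now gives the intervention arm two recruitment periods; include a period term or a sensitivity analysis by period. Women already enrolled benefit only from the analytic part, which cannot remove selection on unmeasured characteristics.

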#### *Masihambisane *Intervention

The Peer Mentors work full-time in the intervention clinics and are integrated into the Department of Health PMTCT programme at each site. WLH are invited to attend a series of four antenatal and four postnatal sessions, scheduled to coincide with their routine antenatal and well-baby clinic visits. Sessions last 60 to 90 minutes, and are attended by four to ten WLH who meet to discuss, roleplay, share, and practice strategies to address issues critical to effective PMTCT. Each session proceeds in a similar sequence: WLH arrive, sing and pray together, and share successes and joys from their week. The Peer Mentor shares her triumphs and challenges as a WLH and acknowledges the importance of the support group for her. A topic is introduced for the day's meeting and a brief demonstration of the content message is presented, then the group brainstorms the types of challenges the WLH will encounter if she tries to implement this knowledge in her life. Finally, goals are set for the upcoming week and a song and a prayer end the meeting.

Each of the following issues is covered by the intervention:

1) *Living Positively*. Using a jar with different coloured jelly beans, the Peer Mentor shows that all families in KwaZulu-Natal are affected by HIV and the WLH is not alone, in particular she has support in the group leader and group members. WLH are encouraged to attend all clinic appointments. Women are provided with referral letters to the couple to encourage them to get tested together for STIs. Women discuss to whom they want to disclose their serostatus and roleplay the process of disclosure and asking for emotional support.

2) *Keeping Myself and My Baby Healthy*. The Peer Mentor helps WLH understand why they must avoid smoking and drinking, eat healthily, take vitamins and medicine as prescribed in antenatal care, get regular exercise, seek and maintain social support, and do things they enjoy. A realistic black baby with Fetal Alcohol Syndrome is presented and the characteristics and life-long consequences of alcohol on babies are discussed. A raw egg is broken in a cup of alcohol and women watch as the egg poaches at room temperature to illustrate adverse effects of alcohol on brain development *in utero*.

3) *Being Prepared*. The PM and WLH discuss the importance of taking medicines, keeping clinic appointments, registering her child to receive the child support grant (models provided and strategies for problem solving challenges to obtaining ID documentation are reviewed), and keeping track of health records. Women are provided a card to give their delivery nurse that says, "I am HIV+, please make sure that I get ART" and women discuss the importance of disclosing status. Additionally, the Peer Mentor demonstrates ART wrapping and appropriate administration method.

4) *Choosing an Exclusive Feeding Method*. WLH are urged to use only one feeding method exclusively for six months, formula feeding is discouraged unless the WLH has clean water on home premises, a toilet, and enough money to buy the product on an ongoing basis. However, clinics do distribute milk powder to all WLH at childbirth. The challenges of using only one feeding method for six months are brainstormed: WLH identify the different types of concerns, such as too little food, ritualistic healing substances, advice from different persons (partner, mother-in-law, neighbors), getting support for child care, and building a strong bond.

5) *Living a Long Life Together*: The steps in obtaining a child support grant are outlined, examples of concrete ways to seek an identity book are provided, the Road to Health card is shown with dates for baby immunizations, healthy meals are presented, pictures of WLH prior to and following ARV (Lazarus effect) are shared, the schedule for getting regular maternal health checkups, including TB tests are outlined, the importance of the six-week HIV test for the baby and returning for results are emphasised, and strategies are reviewed to avoid infecting a partner with HIV.

7) *Being Partners and Parents*. This session stresses getting your partner tested, deciding whether to have another baby, using condoms, dealing with a partner's alcohol use and any multiple partnerships he might have, and finding support for domestic violence.

8) *Enjoying Life*. PM and WLH discuss the importance of taking time for oneself, engaging in pleasant activities for oneself and the baby, maintaining close friendships and other relationships, and asking for and accepting help from others.

Three tools are used in all intervention sessions. To increase awareness and skills for emotional regulation, WLH are taught to use *Feeling Cups *to calibrate their feelings. A clear glass is filled with different levels of water, depending on their degree of uncomfortable (full) feelings. *Tokens *are exchanged between members. These are small chips that indicate positive feelings towards one or more group members. Finally, WLH are provided with an *empty jar and beans *to count the number of times they adhere to their goals.

We have developed a variety of materials, manuals, and videos on PMTCT. Workbooks for pregnant women were adapted for HIV, alcohol and malnutrition content from existing evidence-based interventions [8]. All materials are in Zulu, after being translated and back-translated into English to ensure their accuracy and appropriateness. The colours and images were selected by the intervention team, the Peer Mentors, and the Community Advisory Board. In designing these learning aids, we followed the process for developing materials in Tanzania [38] where "job aids" were developed that are culturally tailored, easy to use, and feasible to distribute. All materials were used in the pilot interventions and we debriefed pregnant WLH, nurses in health clinics, and supervising Peer Mentors in development of the materials to ensure cultural appropriateness.

No incentive is given for participating in the intervention sessions, but participants receive tea and biscuits on arrival, and R30 (about $3.50) towards their transportation costs. Several sessions are held per day at the clinic and are rotated, to enable women to attend any session on the same day as their routine health care appointments. Attendance data is collected at all sessions.

Quality control is managed at three levels: 1) within the clinic by the site coordinator; 2) across clinics by the centralized Intervention Coordinator; and 3) monthly and quarterly by international and domestic intervention specialists. A checklist is completed by the Intervention Coordinator when observing Peer Mentors' groups and provided during routine supervision to Peer Mentors.

